### Statistics

Below, we describe the most probable statistical approaches in the evaluation of associations between self-reported sleep disturbances and exposures. However, in the course of analyses, and with further knowledge of the actual data set, the statistical approach may be supplemented and/or modified. SPSS version 14.0 will be used for statistical analyses. STATA 10 is used for sample size and power calculations.

Age adjustments in groups of subjects with sleep complaints will be performed by the direct method with the Norwegian population serving as standard population.

We plan to carry out series of tabular analyses, tabulating our outcome variables against potential explanatory and confounding variables. These tabulations will guide further analyses. A matched regression analysis will be done using conditional logistic regression in SPSS. For each model we will compare the results of the univariate analyses to those of multivariate analyses. We aim to construct credible parsimonious explanatory models, which will be critiqued using residual analysis, and the Hosmer-Lemeshow goodness of fit test.

Relevant variables that reach significance in bivariate analyzes, will be entered into a multiple logistic regression analyses to determine their influence on sleep outcome variables.

Some of the variables might have missing values. One possible way to deal with missing values is by multiple imputation. To include most of the observations in the model, the missing values may be included after an imputation procedure in SPSS, where the missing value is replaced by the mean of the non-missing values for that variable.

From the first initial screening to the subsequent mapping with the extensive sleep-questionnaire, it may happen that some subjects defined as "cases" reach normal values and vise versa. These subjects and their matched control/case will be excluded from later analyses.

We have calculated sample sizes for three main variables in this study: PSQI, EES and BMI (*p *value for significance = 0.05 (two-sided) and power = 90 %). Ideally, the size of the effect to be detected should be base on clinical judgments, but this is not always straightforward. The effect should be large enough to be clinically important but not so large that it is implausible. We have based our estimates of clinical effects on previous studies of insomniacs compared to healthy controls for PSQI [69], ESS[70]and BMI [20]. We have calculated the standard deviations for each variable (PSQI = 4.58, ESS = 5.9 and BMI = 5.7), and decided that clinically relevant differences for these variables are PSQI > 2, ESS > 2 and BMI > 1. The necessary sample sizes (number of pairs) to detect significant differences between cases and controls are; PSQI = 56 pairs, ESS = 92 pairs and BMI = 342 pairs. Thus, for the three variables above, the planned study seems to be large enough to detect differences between groups.

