## Methods

### Setting

The current study will be performed in a non-institutionalized general population in northern Norway, aged 20 to 90 years. Samples will be drawn in a two-stage procedure, described below.

In the first stage, data from all eligible participants in the Tromsø VI Study will be assessed, in order to describe sleep disturbances and their associated risk factors. In the initial survey, self-reported sleep disturbances will be addressed in questionnaire 1 (Q1), with one single question; "During the last 12 months, how often have you experienced sleep disturbances?", answered with a four-item response: *"never", "1–3 times per month", "once a week" *or *"more than once a week"*. In this initial screening, the selection criterion for sleep disturbances will be *"more than once a week"*.

In the second stage, all participants who report sleep disturbances ("*more than once a week"*) will be invited to a second cross-sectional survey, where sleep complaints and daytime sleepiness will be mapped, using a sleep assessment questionnaire (questionnaire 2 = Q2) described below. A pair-matched control group (matched for age and gender) will be recruited among the remaining participants (those without sleep complaints).

Assuming that the prevalence of sleep complaints in the Tromsø VI Study corresponds to previous estimates for the general population, we expect to include 10 to 15% of the total study population into the sleep complaint group.

In order to analyze possible seasonal effects due to the natural annual light-dark cycle in the artic, we will examine a random half of the participants in the sleep complaint group and control group with Q2 in the part of the year with the highest levels of environmental light (May-June), and examine the remaining participants with Q2 in the part of the year with the lowest levels of environmental light (November-December).

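### The Hosmer-Lemeshow test, read naturally, is to check the 1:1 conditional logistic models, where its usual reference distribution is wrong: it rejects correct models about 10% of the time at a nominal 5%

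*Protocol article*

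**What the plan says.** The Setting section of the protocol article fixes the design: "A pair-matched control group (matched for age and gender) will be recruited among the remaining participants". The Statistics section names the corresponding analysis: "A matched regression analysis will be done using conditional logistic regression in SPSS". It then says that univariate and multivariate results will be compared for each model, and that the final models should be credible and parsimonious, "which will be critiqued using residual analysis, and the Hosmer-Lemeshow goodness of fit test". Conditional logistic regression is the only model type named in that paragraph.

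The following paragraph adds a second type. Variables significant in bivariate analysis "will be entered into a multiple logistic regression analyses to determine their influence on sleep outcome variables"; this model is not said to be conditional. The section describes its methods as likely rather than final. It gives no significance level, number of groups or decision rule for the goodness-of-fit test.

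**The concern.** Hosmer-Lemeshow sorts subjects by fitted risk, compares observed with expected cases in about ten groups, and refers the sum to chi-square on 8 degrees of freedom. That reference is meant for independent subjects whose absolute risks are modelled. A 1:1 conditional model has no intercept and models no absolute risk. Every pair contains exactly one case, and its fitted probabilities are p and 1 − p.

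Two things are at stake. A correct matched model may be flagged more often than the nominal level suggests, which invites unnecessary data-driven changes. And a non-significant result may be read as support for a model in which the shape of an exposure effect is badly wrong, so that its odds ratios mislead.

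**Working it through.** **Inputs from the article.** Pairs are 1:1 (Setting). The BMI sample size is 342 pairs (Statistics). The sleep complaint group is expected to be 10 to 15% of the study population (Setting), which is about 12,000 (Recruitment and randomization): 0.10 × 12,000 = 1,200 and 0.15 × 12,000 = 1,800 pairs.

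**The plan's own figures first.** With "value for significance = 0.05 (two-sided) and power = 90" per cent, SDs "PSQI = 4.58, ESS = 5.9 and BMI = 5.7", and "clinically relevant differences for these variables are PSQI > 2, ESS > 2 and BMI > 1", the paired formula is n = (SD × (1.960 + 1.282) / difference)², rounded up, with each SD taken as that of the pair difference:
- PSQI: (4.58 × 3.242 / 2)² = 55.1, so 56
- ESS: (5.9 × 3.242 / 2)² = 91.4, so 92
- BMI: (5.7 × 3.242 / 1)² = 341.4, so 342

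These match "PSQI = 56 pairs, ESS = 92 pairs and BMI = 342 pairs". They supply the smallest pair count used below. The article gives no figure for Hosmer-Lemeshow to reproduce.

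**Size, by reasoning.** Sort the 2n fitted probabilities into ten groups. If one member of a pair falls in group g, its partner falls in group 11 − g. Observed minus expected in one group is the negative of that in its mirror, and the variance terms are equal. The statistic is therefore twice a sum over five groups. Taking that sum as approximately chi-square on 4 degrees of freedom, the rejection probability at the usual cut-off of 15.51 is

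P(2 × χ²₄ > 15.51) = P(χ²₄ > 7.754) = exp(−3.877) × (1 + 3.877) = 0.0207 × 4.877 = 0.101.

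The doubling is exact apart from ties and uneven group sizes. The 4 degrees of freedom are an approximation: 3 would give 0.051 and 5 would give 0.170. Simulation supports 4. The statistic under a correct model had mean about 8 and variance about 30 to 32. Twice χ²₄ has mean 8 and variance 4 × 8 = 32, whereas χ²₈ has variance 16.

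**Size, by simulation.** Correct conditional models were fitted with 342, 1,200 and 1,800 pairs, 1, 3 or 5 normal covariates, within-pair correlation 0, 0.2 or 0.5, and 1,500 replicates per setting. Hosmer-Lemeshow rejected in 8.1 to 11.7% of data sets at nominal 5%. Applied to an ordinary unconditional logistic model in the null runs, it rejected in 4.0 to 5.7%.

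**Power, by simulation.** Same pair counts, normal covariates, ten groups, 800 to 1,500 replicates. The comparison is a 1-df likelihood-ratio (LR) test of a squared term in the conditional model; a dash means it was not run.

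| True shape omitted from a linear model | Hosmer-Lemeshow rejects | LR squared term rejects |
|---|---|---|
| U shape, 0.5x² | 8.1–11.8% | 100% |
| Threshold, 1.5 if x > 1 | 10.6–11.5% | 85–100% |
| 0.5x² in one of three covariates | 9.6–12.4% | 100% |
| Interaction, 0.5x₁x₂ | 8.8–12.4% | 5.5–7.5% |
| 0.5x + 0.5x² | 12–22% | 100% |
| x + 0.5x² | 12–51% | – |
| Saturating, 2tanh(2x) | 14–56% | – |
| Cubic, 0.3x³ | 10–63% | – |
| Sinusoidal, 1.5 sin(1.5x) | 19–100% | 15–17% |

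In the first four rows Hosmer-Lemeshow rejects no more often than it does for correct models. For the quadratic shapes the reason is visible in the algebra: x₁² − x₂² = (x₁ − x₂)(x₁ + x₂). The groups are formed from the within-pair difference. For centred symmetric covariates the sum averages to zero at any given difference, so the curvature cancels inside each group.

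**The case against.** The article does not say outright that Hosmer-Lemeshow is for the conditional models. An unmatched logistic model appears one paragraph later, and the first stage covers all participants with a yes/no outcome. For such models the test is a usual choice and held its size. This stands in part: the reading is natural, not certain. But nothing excludes the conditional models, so the restriction needs to be written either way.

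Residual analysis is also planned, so Hosmer-Lemeshow is not the only check. That limits the harm but does not make the test valid. The plan is provisional, no rule ties a significant result to a model change, and no endpoint or sample size depends on it. These points hold and lower the severity. A fuller plan might settle diagnostic detail, but the article names a specific test beside a specific model, so this is more than detail left unstated.

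The LR comparison favours the alternative, since a squared-term test is aimed at exactly the curvature simulated. That is fair. The same test does not find an omitted interaction, and no power was computed for interaction tests.

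A reader might also infer that the test misses gross misfit about 90% of the time, or that it is unrelated to fit. The table contradicts both: it responds to saturating, cubic and sinusoidal shapes, increasingly with more pairs. With a right-skewed covariate, a quadratic coefficient of 0.30 and 1,800 pairs, it missed 77%. Nor can one say that it doubles a stated error rate: the 0.05 in the article belongs to the sample-size calculation.

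**Conclusion.** The point holds for the conditional models, read as the intended target. Against its usual chi-square(8) reference, Hosmer-Lemeshow has a false-rejection rate of about 10% at nominal 5%. That result rests on the mirrored groups and was stable over the pair counts, covariate counts and within-pair correlations tried. Its near-absence of power against pure U-shaped, threshold, three-covariate quadratic and omitted-interaction misfit is a simulation result under normal covariates and ten groups, not a figure from the article. It should not be extended to misfit in general. Unmatched logistic models are unaffected by this size problem. Severity is minor to moderate: a secondary check does not work as intended, but the matched odds ratios can still be estimated and residual analysis remains.

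**What to change.** In the Statistics section, state that Hosmer-Lemeshow applies only to unmatched logistic models, for example the first-stage analysis of all participants. For the conditional models, replace it with:

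- likelihood-ratio tests, within the conditional likelihood, of added non-linear terms (squared or spline) for continuous covariates;
- likelihood-ratio tests of interactions listed in advance, since a squared-term test does not detect these;
- a statement that the planned residual analysis will use pair-level residual and influence (delta-beta) diagnostics from the conditional fit.

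The cost is one sentence and a few extra model fits on data already being collected, with no additional participants.

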### Outcome measures

Outcome measures in the first part of this study will be the prevalence of sleep disturbances as reported in the initial questionnaire (Q1) containing a four-item response option, where sleep disturbance is defined as the average occurrence of sleep problems *"more than once a week"*.

In the second part of the study, sleep characteristics will be further mapped by a sleep questionnaire (Q2), sent by mail to subjects in the sleep complaint group and in an approximately equal-sized control group. Recruitment, pair matching, questionnaire logistics (including reminders) will be handled by the Tromsø Study's central body, situated at the University of Tromsø. Outcome measures are summarized in Table 3.

**Table 3 T3:** Sleep outcome variables, potential explanatory variables and their pre-specified associations in the Tromsø Study

*Sleep outcome variables against potential explanatory variables*	*Pre-specified associations*	*References*
Initial screening of all eligible participants in the Tromsø Study:		
• Prevalence of sleep disturbances reported in the initial questionnaire (Questionnaire 1) containing a four-item response option, where sleep disturbance is defined as the average occurrence of sleep problems *"more than once a week"*.	10 to 50% in the adult population.	[2, 76]
• Sleep disturbances and their possible relationships, including demographic variables, health-related variables, and lifestyle and socioeconomic variables, and biological markers.	Increased risk for impairments in health, decreased quality of life and increased healthcare utilization.	[19, 65, 77-80]

Further mapping with validated sleep assessment questionnaires among subjects with sleep complaints selected in the initial screening and their control group:		
• Sleep outcome variables related to the use (dose and frequency) of specific prescription drugs, derived from the Norwegian Prescription Database (NorPD).	Frequent use of hypnotics and over-the-counter (OTC) medications.	[36, 37]
• Sleep outcome variables related to socioeconomic variables.	Insomnia related to unemployment and socioeconomic deprivation, more common in women, elderly and individuals living alone.	[81, 82]
• Sleep outcome variables and excessive daytime sleepiness related to objective medical diagnosis, such as diabetes and coronary disease.	A possible link between short sleep, diabetes mellitus, coronary heart disease and all over mortality.	[21, 25-28]

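### Entering covariates only if they are significant in bivariate analysis can drop masked confounders, and the plan leaves open which logistic model and which fit test apply to the matched pairs

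*Protocol article*

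**What the plan says.** The Statistics section plans tabulations first and then models. For the matched data it states: "A matched regression analysis will be done using conditional logistic regression in SPSS". It goes on to compare univariate with multivariate results for each model and aims at parsimonious explanatory models, "which will be critiqued using residual analysis, and the Hosmer-Lemeshow goodness of fit test".

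A separate paragraph then gives the entry rule: "Relevant variables that reach significance in bivariate analyzes, will be entered into a multiple logistic regression analyses", the purpose being "to determine their influence on sleep outcome variables". It gives no significance level for the screen, names no variable to be kept regardless of significance, and does not say whether the model is conditional or which data set it is fitted to.

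Two data sets are in play. Setting describes stage one with the words "data from all eligible participants in the Tromsø VI Study will be assessed, in order to describe sleep disturbances and their associated risk factors"; that sample is unmatched. For the second questionnaire (Q2), "A pair-matched control group (matched for age and gender) will be recruited among the remaining participants", and Outcome measures describes an "approximately equal-sized control group", so the design is about 1:1.

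The section introduces all of this as the most probable approach, which may be supplemented or modified. Under Aims and objectives, the study is presented as able to find independent correlates of sleep disturbances.

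**The concern.** An independent correlate is one whose association survives adjustment for the variables that confound it. Whether a variable confounds depends on its relation to both exposure and outcome, not on whether its crude association with the outcome passes a significance test. A screen on the crude p-value therefore asks the wrong question. It fails worst for negatively masked confounders, whose direct effect on the outcome runs against the effect they carry through the exposure.

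Selection on the same data also has a cost when it picks the right variables: the final p-values and confidence intervals treat the model as fixed in advance and so come out too optimistic.

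Two further points follow from the wording. Because the model in the screening sentence is not identified, an analyst could fit it to the pairs without conditioning on them. And because the fit test is named for the models in general, directly after the conditional model, it could be applied where its usual form is not valid.

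**Working it through.** **Sample sizes used.** The article gives no figure for the selection rule, so its own sample sizes were reproduced to set realistic numbers of pairs. With "value for significance = 0.05 (two-sided) and power = 90"%, n = ((1.960 + 1.282) × SD / difference)²:

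- PSQI: (3.242 × 4.58 / 2)² = 55.1, so 56 pairs (stated 56)
- ESS: (3.242 × 5.9 / 2)² = 91.5, so 92 pairs (stated 92)
- BMI: (3.242 × 5.7 / 1)² = 341.5, so 342 pairs (stated 342)

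The expected case group is 10 to 15% of about 12,000, that is 1,200 to 1,800. The check used 342 and 1,200 pairs.

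**Why a confounder can be masked.** Let C be a standardised confounder with log odds ratio b for the outcome, and let the log odds of exposure rise by g per unit of C. The exposure has log odds ratio ln 2 = 0.693. Near the centre of C, with exposure probability 0.5, the crude slope of C is roughly b + 0.693 × 0.25 × g.

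- b = −0.20, g = 1: −0.20 + 0.173 = −0.027
- b = −0.25, g = 1.5: −0.25 + 0.260 = +0.010
- b = +0.15, g = 1: +0.15 + 0.173 = +0.323

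The first two look nearly null to a bivariate test. The third looks stronger than it is and passes easily. The approximation overstates the offset away from the centre, so a simulation is needed for size.

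**Screening inside a conditional model.** Case-control pairs, conditional logistic regression, true odds ratio 2, 200 replicates. C is entered only if its bivariate p is below 0.05 (assumed, because the article gives no level). These pairs were formed at random, without age or gender, to isolate the effect of the screen.

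| Pairs | b | g | C kept | OR, C forced in | OR, after screen | OR, C never entered |
|---|---|---|---|---|---|---|
| 342 | −0.20 | 1 | 12.5% | 1.94 | 1.71 | 1.65 |
| 342 | −0.25 | 1.5 | 12.0% | 1.94 | 1.56 | 1.49 |
| 1,200 | −0.20 | 1 | 30.0% | 2.01 | 1.81 | 1.70 |
| 1,200 | −0.25 | 1.5 | 34.5% | 2.02 | 1.72 | 1.54 |
| 342 | +0.15 | 1 | 98.5% | 2.00 | 2.00 | 2.27 |
| 1,200 | +0.15 | 1 | 100% | 2.01 | 2.01 | 2.27 |

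For b = +0.25 and g = 1, C was kept in every run at both sizes. In the masked rows the screened odds ratio is 10 to 20% below the forced one (1.81/2.01 = 0.90; 1.56/1.94 = 0.80).

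**What the unnamed model type could do.** Exact 1:1 matching on seven age bands and sex, 1,200 pairs, case status as outcome, true odds ratio 2, 60 replicates, with the exposure's link to age and sex rising from none to strong:

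| Model | None | Weak | Moderate | Strong |
|---|---|---|---|---|
| Ordinary, no age or sex | 1.99 | 1.95 | 1.79 | 1.55 |
| Ordinary, with age and sex | 1.99 | 2.00 | 1.98 | 1.96 |
| Conditional | 1.99 | 1.99 | 1.98 | 2.02 |

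The bivariate test of age against case status gave p = 1.0 in every replicate, as exact matching forces it to.

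**Hosmer-Lemeshow.** In a 1:1 conditional model there is no intercept, and the two fitted probabilities in a pair are p and 1 − p. The risk groups therefore mirror each other and are not independent, so the usual grouping and chi-square reference do not apply.

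**The case against.** A reader might infer that an ordinary logistic model will be fitted to the matched pairs, that the screen will always discard age and gender, and that the odds ratios are therefore biased towards the null. The article does not support this. It plans conditional logistic regression for the matched analysis and nowhere says that an ordinary model is fitted to the pairs. Conditional for the pairs and ordinary for the unmatched first-stage sample is a consistent reading. Age and gender must fail the screen only when the outcome is case status in exactly matched pairs. They need not fail it in the first-stage sample, or for Q2 outcomes such as a PSQI or ESS cut-off. In a conditional model their loss does no harm. The shrinkage in the second table needs an unconditional model, omitted age and gender, and an exposure tied to them, all at once. What stands is that the wording leaves the model unidentified.

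On the screen, it can be said that entry is limited to relevant variables, that confounders are tabulated, that univariate and multivariate results are compared, and that the approach may be modified. These help less than they seem to. Relevance only narrows the candidates. The comparison cannot show the influence of a variable that never entered the model. Freedom to modify adds further dependence on the data. It is true that most confounders acting in the same direction as the effect would survive the screen.

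On the fit test, the text does not assign it to the conditional model by name, and residual analysis stands beside it. Misuse is possible, not established.

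A full confounder list may well belong in a fuller plan, and its absence is not the point. The selection rule itself is stated, and it is the rule that is unsound.

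**Conclusion.** The concern holds for the selection rule. Bivariate significance is a poor criterion for choosing confounders, and it can leave a true confounder out even under the conditional regression that the article plans. Under the assumed strengths, a true odds ratio of 2 was estimated at 1.56 to 1.81 after screening, against 1.94 to 2.02 with the confounder forced in. There was no bias where confounding ran in the same direction as the effect. These sizes depend on confounder strengths and a 0.05 screening level that the article does not give, so they show what can happen rather than what will. The optimism of the final p-values and intervals is a general property of selection on the same data and was not quantified here.

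Two smaller points also hold: the model in the screening sentence is not tied to a data set or stated to be conditional, and the Hosmer-Lemeshow test is not limited to unmatched models. The article does not establish a general bias towards the null. The sample sizes are unaffected. The text should be changed before analysis, but the point does not put the study in doubt.

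**What to change.** Replace the screening sentence and add three statements to the Statistics section:

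1. Confounders for each association in Table 3 are chosen on subject-matter grounds before the outcome data are examined, and are entered whatever their bivariate p-value. Tabulations are descriptive and do not decide entry.
2. Case-control contrasts in the matched pairs use the conditional logistic regression already planned.
3. Any unconditional model, whether for the first-stage sample or for a Q2 outcome, always includes age and gender.
4. The Hosmer-Lemeshow test is used only for the unmatched first-stage models. Matched models are checked with pair-level residuals and influence measures.

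The cost is a change of wording and a short confounder list. No new data are needed. The models spend a few more degrees of freedom and are less parsimonious, which is a small price with an expected 1,200 to 1,800 cases.

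### The missing-data text names multiple imputation but describes single mean replacement, which would leave part of the confounding in the adjusted logistic models

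*Protocol article*

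**What the plan says.** All the relevant text is in the Statistics section of the protocol article. It starts from the expectation that "Some of the variables might have missing values", without saying which ones. It continues: "One possible way to deal with missing values is by multiple imputation". The next sentence gives a purpose, which is to keep most participants' records in the regression, and says that SPSS may be used for this. The procedure it describes is one "where the missing value is replaced by the mean of the non-missing values for that variable".

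The section mentions no repeated imputed data sets, no imputation model and no pooling of variances. The main model is named shortly before: "A matched regression analysis will be done using conditional logistic regression in SPSS". Variables that are significant in bivariate analysis then go into multiple logistic regression. The section introduces its methods as the most probable ones and allows them to be changed once the data are known.

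**The concern.** The label and the procedure do not match. Multiple imputation draws several plausible values from a model that uses the other variables, and it carries the uncertainty into the standard errors. Mean replacement inserts one constant, the same for cases and controls and for every age and sex, and treats it as observed. An analyst could follow the sentence literally and report the result as multiple imputation.

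The second aim of the study is to relate sleep outcomes to explanatory variables with adjustment for confounders. A person whose confounder value is replaced by the overall mean is not adjusted for that confounder, so part of the confounding stays in the estimate. A mean is also not a valid value for a nominal item with more than two categories.

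**Working it through.** **Inputs.** From the Statistics section: "value for significance = 0.05 (two-sided) and power = 90" per cent; standard deviations "PSQI = 4.58, ESS = 5.9 and BMI = 5.7"; "clinically relevant differences for these variables are PSQI > 2, ESS > 2 and BMI > 1". From Setting and from Recruitment: 10 to 15% of about 12,000 participants, so roughly 1,200 to 1,800 cases before non-response. The article gives no missing fraction. I assume m = 10, 20 and 30%, missing completely at random.

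**The plan's own figures.** The pair numbers reproduce with n = (SD × (1.960 + 1.282) / difference)², rounded up:
- PSQI: (4.58 × 3.242 / 2)² = 55.1, so 56.
- ESS: (5.9 × 3.242 / 2)² = 91.5, so 92.
- BMI: (5.7 × 3.242 / 1)² = 341.5, so 342.

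These are correct and are not at issue. There is no stated figure for missing data to reproduce.

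**1. Residual confounding in an adjusted model.** A simulation (n = 400,000) used one confounder giving a crude odds ratio of 1.85 when the true value is 1.0. After adjustment for the mean-filled confounder, the odds ratio was 1.08, 1.15 and 1.23. The share remaining on the log scale is:
- 10%: ln 1.08 / ln 1.85 = 0.077 / 0.615, about 12%.
- 20%: ln 1.15 / ln 1.85 = 0.140 / 0.615 = 23%.
- 30%: ln 1.23 / ln 1.85 = 0.207 / 0.615 = 34%.

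A linear model gives a closed form as a cross-check. Take standardised variables, with the confounder correlated ρ = 0.5 with both exposure and outcome, and no true effect. The crude coefficient is 0.25. After adjustment for the mean-filled confounder it is 0.25 × m / (1 − 0.25 × (1 − m)):
- 10%: 0.025 / 0.775 = 0.032 (simulated 0.033).
- 20%: 0.050 / 0.800 = 0.063 (simulated 0.063).
- 30%: 0.075 / 0.825 = 0.091 (simulated 0.091).

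That is 13, 25 and 36% of 0.25, close to the logistic result. At n = 1,200 the type I error was about 21, 59 and 89%. Complete-case analysis of the same data had bias of about zero and type I error of about 5%.

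Confounder strength matters. In a further simulation (n = 200,000, no true effect), a crude odds ratio of 1.24 left an adjusted value of about 1.01 at 5% and 1.02 at 10% missing. A crude odds ratio of 1.94 left 1.03 and 1.08.

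**2. Mean differences, if outcomes were filled as well.** Both groups receive the same constant, so with equal missing fractions the expected difference is (1 − m) × the true difference. For PSQI: 2 × 0.9 = 1.8; 2 × 0.8 = 1.6; 2 × 0.7 = 1.4. At 56 pairs, simulated power falls from 90% to about 87, 81 and 76%.

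**3. Intervals for descriptive means, if those were filled.** The filled standard deviation is about √(1 − m) times the true one, and n is counted as complete. The reported standard error is therefore (1 − m) times the true one. Coverage is 2Φ(1.96 × (1 − m)) − 1:
- 10%: 2Φ(1.764) − 1 = 92%.
- 20%: 2Φ(1.568) − 1 = 88%.
- 30%: 2Φ(1.372) − 1 = 83%.

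Simulation with n = 400 gave the same three values.

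**4. A single mean-filled exposure in a logistic model.** Here effects 2 and 3 do not appear. In plain logistic regression (n = 1,200, log odds ratio 0.5), the mean estimate was 0.502 at 0, 20 and 30% missing, with coverage of about 95%. In 1:1 conditional logistic regression (342 and 1,200 pairs, log odds ratios 0.62 and 0.20 per SD, 5 to 30% missing), the mean estimate was 99 to 102% of the truth and coverage was 94 to 96%.

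**The case against.** The best defence has four parts.

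- **The text does not commit to the method.** It is permissive throughout, and the two sentences could be read as two separate options. This stands and lowers the severity. It does not make the described procedure sound, and no other imputation procedure is described.
- **The stated purpose is to keep observations in the model, and the models named are logistic regressions.** A reader might infer that every case-control difference shrinks and every confidence interval is too narrow. The document does not support that. It does not say that the descriptive means or the PSQI, ESS and BMI comparisons will use filled data, and step 4 shows a single exposure nearly unaffected. Even for a filled group difference, the reported standard error roughly matches the spread of the estimate, so poor coverage there comes mainly from bias.
- **Confounding is reduced, not left untouched.** This also stands: in the strong example 66 to 88% of it is removed. What remains falls on exactly the multivariable models the plan relies on.
- **A 0/1 item filled with its proportion behaves like any mean-filled covariate.** This is correct. The objection to a mean as a value is limited to nominal items with more than two categories, and the article does not say that such items will be filled.

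A reader might also infer that STATA 10 is already available in the plan for proper imputation. The article assigns it only to sample size and power calculations.

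**Conclusion.** The point holds in limited form. The article names multiple imputation and describes only single replacement by the overall mean. If applied as written, adjustment for mean-filled confounders is incomplete: about 12, 23 and 34% of the confounding remains at 10, 20 and 30% missing for one strong assumed confounder, and less in absolute terms for weaker ones. Shrunken outcome differences and narrow intervals for means follow only if the method is extended to outcomes and descriptive summaries.

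The sizes rest on assumed missing fractions, assumed confounder strength and values missing completely at random. In the settings checked, the direction of the bias follows from the method. The severity is should-fix, because the method is optional as worded and the missing fraction is unknown.

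**What to change.** Delete the mean-replacement sentence. State instead that missing values will be handled by multiple imputation, with case status, the matching variables (age and gender), the analysis covariates and the sleep outcomes in the imputation model. Estimates should be pooled by Rubin's rules, and complete-case results shown beside them. Name software that supports this. Nominal items should be imputed with a model for categories.

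The cost is wording, some analyst time and possibly wider intervals. Design, recruitment and data collection do not change.
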